#### Main secondary outcomes

Somatic, depressive, and anxiety symptoms will be evaluated using the German version of the Patient Health Questionnaire Somatic Symptom Scale 15 (PHQ-15), the Patient Health Questionnaire Depression Scale 9 (PHQ-9), and the Generalized Anxiety Disorder Scale-7 (GAD-7) [49–51]. To assess fatigue, we will use the Fatigue Severity Scale (FSS) [52]. Post-exertional malaise will be measured by an adapted German version of the DePaul Post-Exertional Malaise Questionnaire (PEM). The five DSQ PEM items assess the frequency and severity of PEM over a six-month timeframe. Five additional PEM items examine the duration of symptom exacerbation after activity (3 items), whether patients perceived physical and cognitive exhaustion, and whether participants were not exercising because it made their symptoms worse [53, 54]. Sleep disturbances will be quantified using the Insomnia Severity Index (ISI), a validated measure of insomnia severity and its impact on daily functioning [55, 56]. Social support, a key factor in coping with illness and adversity, will be assessed using a validated German version of the ENRICHD Social Support Instrument (ESSI), which captures perceived social support [57]. The short version of the Sense of Coherence Scale (SOC-3) will be used to assess the participants’ perceived ability to cope with stressors and maintain a sense of coherence and meaning in their lives [58]. Perceived stress levels will be measured using the Perceived Stress Scale (PSS-4), a short version of the 14-item Perceived Stress Scale, a widely used instrument for assessing the degree to which situations in one’s life are appraised as stressful [59]. Furthermore, psychological stress specific to somatic symptoms disorder (SSD-12) will be evaluated to capture the stress experienced in response to physical symptoms [60]. Participants’ coping strategies in response to PASC symptoms will be evaluated using the Patient Competence in Coping with Cancer Questionnaire (PUK-2) adapted for PASC symptoms. This measure aims to assess the perceived competence of participants to manage and cope with the challenges posed by ongoing symptoms [61]. Finally, patients’ health-related quality of life will be measured by using the SF-36 [62].

The neuropsychological test battery will consist of the following validated assessments: the Verbal Learning Memory Test (VLMT) [63], the Digit Span Backwards from the Wechsler Memory Scale-Revised (WMS-R) [64], the Trail Making Test (TMT) Parts A and B [65], the d2 Test of Attention [66], and the Regensburger Verbal Fluency Test (RWT) [67]. The VLMT evaluates verbal memory, including delayed free recall (the retention of learned words over time) and recognition ability. The Digit Span Backwards subtest from the WMS-R measures working memory. The TMT assesses visuomotor processing speed, attention, and executive functions such as mental flexibility. The d2 Test of Attention measures selective attention and processing speed. The RWT evaluates both formal lexical (phonemic) fluency and semantic fluency, which are indicators of divergent thinking.

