In order to appropriately tackle all these issues of PASC, an integrated multimodal approach in a psychosomatic treatment setting is ideal. In our trial, we are testing this inpatient psychosomatic PASC setting for effectiveness with a control group. Key endpoints include changes in the severity of PASC (primary outcome), as well as overall physical and mental health symptoms such as insomnia, fatigue, PEM, neurocognitive impairments, anxiety, and depression (secondary outcomes). Additional secondary outcome measures include perceived social support, distress, sense of coherence, quality of life, and coping with illness. Moreover, outcomes like healthcare utilization and treatment satisfaction are assessed.

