### Study design

This is a prospective non-randomized controlled trial. It is a two (group: intervention and control) by three (time: pre-treatment, 5 weeks, 6 months) repeated measures factorial design. The overall study design is illustrated in Fig. 1 and Table 1. In T0 sociodemographic data, medication, and use of previous psychotherapeutic inpatient or outpatient treatments, as well as data on health behavior (e.g. smoking, alcohol consumption, etc.) of the patients will be collected. Participants in the intervention group will complete a comprehensive web-based questionnaire battery at three time points: at the time of admission to the hospital setting (T0), at the end of inpatient treatment five weeks later (T1), and 6 months after discharge from the hospital setting (T2). The control group will accomplish the questionnaire within a time frame of around 6 months after presentation at the Post-COVID Center of the Universitätsklinikum Erlangen (T0), five weeks after T0 (T1), and 6 months after T0 (T2). The questionnaires at T0, T1, and T2 will be made available web-based via a link and a password. Participants who drop out of the intervention or control group will be reported in the final results. Before participation, written informed consent must be given. A schematic overview of the trial flow is given in Fig. 1. The instruments used at each time point are displayed in Table 1.

**Table 1 Tab1:** Overview of the assessment schedule for both groups

Measures	Assessment time points		
	Baseline (T0)	5 weeks later (T1)	6-month follow-up (T2)
Sociodemographic variables	X		
Health behavior	X	X	X
Use of PASC-specific treatments		X**	X
Use of PASC-specific outpatient or inpatient psychotherapeutic treatment	X	X**	X

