**Secondary outcomes**			
Somatic, Depression, and Anxiety symptoms (PHQ-15; PHQ-9; GAD–7)	X	X	X
Sleep (ISI)	X	X	X
Fatigue (FSS)	X	X	X
Post-exertional malaise (PEM)	X	X	X
Social support (ESSI)	X	X	X
Sense of coherence (SOC-3)	X	X	X
Distress (PSS-4)	X	X	X
Somatic symptom disorder (SSD-12)	X	X	X
Patients’ competence to cope with illness (PUK-2)	X	X	X
Quality of life (SF-36)	X	X	X
Satisfaction with treatment			X*

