### Intervention

The intervention consists of a five-week inpatient psychosomatic treatment according to an integrative comprehensive concept of depth psychological and cognitive-behavioral therapy. The patients will be admitted in closed groups of 5 to 6 patients each.

All therapists will be physicians in advanced or completed specialized training in psychosomatic medicine and psychologists in advanced or completed training in clinical psychotherapy, physiotherapists, registered nurses, social workers, and psychotherapists for integrative body and movement therapy. At the beginning of the study, all therapists will receive several training courses on psychosomatic aspects of PASC, the PASC guideline, the PASC concept for inpatient psychotherapy, immunological principles of PASC and fatigue, and the treatment of PASC in physiotherapy and aerobic exercise therapy.

We have adopted parts of the concept from the working group of Köllner et al. [44] and adapted it to our psychosomatic inpatient setting. The psychotherapeutic focus of the treatment is on coping with the PASC symptoms and treating comorbid mental symptoms that have arisen as a result of the chronic illness. Table 2 provides an overview of the treatment interventions, addressing the key aims of each element. Four cornerstones of treatment are applied in addition to our regular multimodal, focus-orientated psychotherapy concept. Figure 2 illustrates these cornerstones, which are explained in detail below.

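### The five DSQ PEM items use a six-month timeframe but are scheduled five weeks after baseline, so about 80% of their T1 window predates T0 and change on them is pulled towards zero

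*Protocol article*

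**What the plan says.** Under Main secondary outcomes, the protocol article describes a PEM questionnaire with two parts. For the first: "The five DSQ PEM items assess the frequency and severity of PEM over a six-month timeframe". For the second: "Five additional PEM items examine the duration of symptom exacerbation after activity (3 items"), plus exhaustion and not exercising because symptoms get worse. No recall period is given for this second part.

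Table 1 marks PEM at T0, T1 and T2. Under Study design, the intervention group's later assessments are "at the end of inpatient treatment five weeks later (T1), and 6 months after discharge from the hospital setting (T2"). The control group's are "five weeks after T0 (T1), and 6 months after T0 (T2"). Under Intervention: "The intervention consists of a five-week inpatient psychosomatic treatment". T1 is thus five weeks after T0 in both groups.

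The Introduction counts PEM among the "overall physical and mental health symptoms such as insomnia, fatigue, PEM, neurocognitive impairments, anxiety, and depression (secondary outcomes"). The article calls the instrument an adapted German version but states no shorter recall period for T1.

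**The concern.** A recall window much longer than the interval between two visits makes the second answer largely a repeat of the first. Here the T0 and T1 windows of the five DSQ items mostly cover the same weeks, and in the intervention group those shared weeks come before admission.

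PEM is the symptom most directly tied to the possible benefit or harm of exercise with pacing. The Introduction argues that aerobic exercise combined with pacing can be used without provoking PEM, and the Intervention section makes avoiding PEM a focus of psychoeducation. T1 is the assessment at the end of that programme. If the five items barely move between T0 and T1, a reader could take this as no effect, or as reassurance about exercise, when the items had little room to show either.

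**Working it through.** **Inputs**
- Recall window of the five DSQ items: six months, about 26 weeks (Main secondary outcomes). Taking a month as four weeks gives 24.
- T0 to T1: 5 weeks in both groups (Study design).
- T2: six months after discharge (intervention), six months after T0 (control) (Study design).
- Evaluable number: 49 per group; two-sided 5% level; correlation 0.5 (Sample size calculation and statistical methods).
- Assumed here, not in the article: a true standardised PEM difference of 0.5, present throughout the five weeks after T0.

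**The plan's own figure.** The article gives no power or sample size for PEM. Its N of 98 is for the PCS Score. It reproduces from the between-groups repeated-measures F test with f = 0.25, correlation 0.5 and three measurements: noncentrality 98 × 0.25² × 3 / (1 + 2 × 0.5) = 9.19, power 0.851. It serves below only as the source of 49 per group.

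**Window at T1**
- Share after T0: 5/26 = 19.2%. Share before T0: 21/26 = 80.8%.
- With 24 weeks: 5/24 = 20.8% after and 19/24 = 79.2% before.
- The T0 and T1 windows share about 21 of 26 weeks.

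**Window at T2**
- Intervention: starts at discharge.
- Control: starts at T0.
- Neither contains time before T0.

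**Illustrative size at T1.** If the five weeks after T0 carry weight w in the answer, the visible difference is 0.5 × w. The SD of change is taken as √(2 × (1 − 0.5)) = 1 in units of the cross-sectional SD; the correlation of 0.5 is borrowed from the PCS Score. By normal approximation, power = Φ(d√(n/2) − 1.96), with n = 49 and √(49/2) = 4.95.

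| Recall model (assumed) | w | Visible d | Power |
|---|---|---|---|
| Even averaging over 26 weeks | 0.192 | 0.096 | Φ(0.476 − 1.96) = 0.069 |
| Recent five weeks carry half the weight | 0.5 | 0.25 | Φ(1.237 − 1.96) = 0.235 |
| No dilution | 1 | 0.5 | Φ(2.475 − 1.96) = 0.697 |

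Adding the opposite rejection tail to the first row, Φ(−1.96 − 0.476) = 0.007, gives 0.076; hence about 7–8%. A worsening of the same size would be masked to the same degree.

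**The case against.** **The illustration leans towards the pessimistic end.** Under strict even averaging, the 21 shared weeks cancel: T1 minus T0 equals 5/26 times the difference between the five weeks after T0 and the oldest five weeks of the T0 window. Symptom variation in the change score then shrinks along with the signal, and only response error and coarse answer categories dilute the standardised effect. The article quantifies neither. This stands: 0.10 and 7–8% are a worst case among the models shown, not an estimate.

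**Only part of the questionnaire is involved.** A reader might infer that PEM as a whole cannot be interpreted at T1. The article does not support that, because the six-month timeframe is stated for five items and no window is given for the other five.

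**Little formally depends on it.** PEM is a secondary outcome, the secondary hypothesis does not name it, and no specific T1 test of PEM is described. This limits the importance of the point but does not remove the mismatch.

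**Worsening could be seen elsewhere.** Fatigue and somatic symptoms are also measured at T1. Symptoms and exertion are rated during physical therapy, there are weekly medical consultations, and unexpected adverse events are documented. A reader might infer that harm would go unseen; that goes too far. None of these is a controlled comparison of PEM, however.

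**The wording at each visit is not visible.** The questionnaire is not shown, and the sentence may describe the source items in general. That is possible, but the article states six months and nothing shorter, so the schedule has to be judged against it.

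**Conclusion.** The point holds for the five DSQ frequency and severity items at T1. About 80% of their window (79–81%, depending on how six months is converted to weeks) predates T0. The direction follows from the overlap: T0–T1 change and the group difference are pulled towards zero. The amount does not follow from the article. A true difference of 0.5 would appear as roughly 0.10 to 0.25 under the two diluting recall models, and those figures rest on the assumed effect, the assumed recall weights and an SD of change of 1.

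T2 does not share the problem. The primary PCS Score analysis and the sample size are untouched. The reason to act is that T1 is where a benefit or harm of the programme on PEM would first be looked for, and an unchanged score there would say little.

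**What to change.** **Preferred.** Keep the six-month wording. Name T2 as the time point for comparing groups on the five DSQ items. State that an unchanged T1 score on these items is evidence neither of no effect nor of safety. The other five PEM items can stay at T1; stating their recall period would settle whether they are affected. This needs no change to the questionnaire or the visits. The cost is that the trial has no usable end-of-treatment comparison on these five items.

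**Alternative.** Give the five items a recall period of at most five weeks, identical at T0, T1 and T2 in both groups, so that no T1 window reaches back before T0. The costs are less comparability with the published six-month version and with T0 data already collected, and a T1 window that lies wholly within the inpatient stay for the intervention group but not for controls.

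The different anchoring of T2 in the two groups (discharge versus T0) affects every outcome. It is a separate matter, and this fix does not require the control group's T2 to move.

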#### Participant timeline

The schedule of the study including enrollment, intervention, and data assessment is given in Fig. 1 and Table 1.

#### Data collection, data management, and data storage

Study data will be collected using Heartbeat Medical [68] and REDCap (Research Electronic Data Capture) [69, 70]. Data collection will take place within the clinic and will comply with the legal data protection conditions of the EU GDPR (European Union General Data Protection Regulation). The links for the questionnaires will be personalized, with a password sent by post to activate the link. To obtain the most complete data possible, patients are reminded twice to complete the questionnaires. Data will only be stored and processed in encrypted form. Each participant will be given a research number, so it will not be possible for outsiders to link the data to the individual. Only those responsible for the study, who are bound by medical confidentiality, will have access to a list of personal data and corresponding research numbers. This list will be kept under lock and key. The data will be published anonymously.

#### Sample size calculation and statistical methods

Sample size calculation was performed with G*Power Version 3.1.9.7 [71, 72]. The sample size calculation is based on testing the primary hypothesis that inpatient psychosomatic treatment leads to a significantly lower mean PCS Score across the first two follow-up assessments (T1 and T2) as compared to treatment as usual. Because of the novelty of PASC, data on our primary outcome, the PCS Score, were not available in this population over different time points. Therefore, we assumed a conservative correlation of 0.5 among repeated measurements and a medium effect size. Based on a medium effect size (f = 0.25) and a power of 85%, a sample size of 98 participants is required, with 49 participants per group. Assuming a conservative dropout of 20%, we will randomize 118 participants, 58 for each condition.

We will perform standard techniques of data preparation with tests of normality and homogeneity and with imputation of missing data in the case of dropouts. Furthermore, we will conduct different descriptive analyses of sociodemographic and medical data. The primary statistical analyses will be a two-way mixed-design Analysis of Variance (ANOVA) with the independent variables being condition (treatment vs. treatment as usual) and time (T0, T1) and condition by time interaction as fixed effects as well as repeated measures ANOVA for the follow-up measurement with repeated measurements. Additionally, we will perform regression analyses to identify potential predictors of treatment outcomes. In all analyses, two-sided p values of < 0.05 are considered to indicate statistical significance. All analyses will be conducted using the statistical software SPSS.

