### Primary hypothesis

We expect the intervention to be superior to treatment as usual (TAU) regarding a significantly lower mean of PASC symptoms measured by the Post-COVID Syndrome Scale (PCS Score) post-treatment and at 6 months follow-up.

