### Outcomes

#### Primary outcome

The primary outcome are symptoms of PASC at the end of the treatment (T1, see Table 1). To measure those, we will use the PCS-Score. The PCS-Score consists of 12 yes/no questions and covers the entire spectrum of possible PASC symptoms. Each question is given its weighting factor, which assigns a meaning to the corresponding symptom complex. The resulting sum score ranges from 0 (= complete absence of any symptoms) to 59 (= presence of symptoms in each of the 12 symptom complexes). A clinically relevant PASC can be assumed from a PCS Score of 26.25 (high PCS Score). Values between 10.75 and 26.25 indicate an intermediate or moderate PASC. The PCS Score was validated on a German population [48].

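### The primary endpoint is given as T1 in one place and as T1 and T2 in others, and the 85% power quoted for N = 98 belongs to neither the T1/T2 mean nor the T0–T1 interaction test

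*Protocol article*

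**What the plan says.** All references are to the protocol article.

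- **Primary outcome:** "The primary outcome are symptoms of PASC at the end of the treatment", identified there as T1 and measured by the PCS Score.
- **Primary hypothesis:** a lower mean of PASC symptoms on the PCS Score "post-treatment and at 6 months follow-up".
- **Sample size calculation and statistical methods, basis of N:** the calculation is said to test the primary hypothesis of a "significantly lower mean PCS Score across the first two follow-up assessments (T1 and T2) as compared to treatment as usual".
- **Same section, inputs:** "Based on a medium effect size (f = 0.25) and a power of 85%, a sample size of 98 participants is required", 49 per group. On the correlation: "we assumed a conservative correlation of 0.5 among repeated measurements and a medium effect size". On significance: "two-sided p values of < 0.05 are considered to indicate statistical significance". G*Power is named, but not the test chosen in it or the number of measurements entered.
- **Same section, analysis:** the primary analyses are in the plural. The first is a "two-way mixed-design Analysis of Variance (ANOVA) with the independent variables being condition (treatment vs. treatment as usual) and time (T0, T1"), including the condition-by-time interaction. It is joined to a repeated measures ANOVA for the follow-up, and the text does not rank the two.
- **Study design:** two groups by three times (T0, T1, T2).

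**The concern.** The outcome section makes T1 the endpoint. The hypothesis and the sample-size text bring in T2, and the sample-size text works with an average of the two. The first analysis listed compares change from T0 to T1. These are different quantities with different variances, so one pair of figures (98 participants, 85% power) cannot serve them all.

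Two things are at stake. The power claim may not describe the test on which the trial is judged. And because no section says which result decides, a report could lead with T1, with T2 or with their mean, and cite this protocol for each.

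**Working it through.** **Inputs** (Sample size calculation and statistical methods): f = 0.25, which for two equal groups is d = 2 × 0.25 = 0.5; correlation ρ = 0.5; two-sided α = 0.05; power 85%; N = 98, 49 per group. Number of measurements m: not stated, so m = 1, 2 and 3 were tried.

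**1. Reproducing 98.** G*Power, repeated measures, between factors: λ = f²·N·m / (1 + (m − 1)ρ), with 1 and N − 2 degrees of freedom.

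| m | λ at N = 98 | Power at 98 | Smallest even N for 85% |
|---|---|---|---|
| 3 (T0, T1, T2) | 0.0625 × 98 × 3 / 2 = 9.19 | 85.1% | 98 |
| 2 (T1, T2) | 0.0625 × 98 × 2 / 1.5 = 8.17 | 80.8% | 110 |
| 1 (T1 only) | 0.0625 × 98 = 6.125 | 68.8% | 146 |

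The m = 3 row matches exactly (N = 96 gives 84.4%). One-sided versions need 118, 88 and 80 for m = 1, 2 and 3, so they do not give 98 either.

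**2. The interaction, with f = 0.25 entered as G*Power's interaction f.** λ = f²·N·m / (1 − ρ) = 0.0625 × 98 × 2 / 0.5 = 24.5 for m = 2. Power at 98 is 99.8%, and 38 participants suffice (32 for m = 3). On this scale f = 0.25 means a difference in change of 4 × 0.25 = 1 SD.

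**3. The T0–T1 interaction, with f = 0.25 read as a 0.5 SD difference at T1 and none at T0.** This is a comparison of change scores. The SD of change is √(2(1 − ρ)) = 1 SD at ρ = 0.5. The noncentrality is 0.5 × √(49/2) = 2.475, and power is 68.8%. For 85%, 146 are needed.

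**4. Dependence on ρ** (98 analysed, d = 0.5, no baseline difference). The noncentrality is 2.475 divided by the SD shown, in units of the outcome SD.

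| Test | SD | ρ = 0.3 | ρ = 0.5 | ρ = 0.7 |
|---|---|---|---|---|
| Mean of T1 and T2, between groups | √((1 + ρ)/2) | 86.0% | 80.8% | 75.7% |
| T0–T1 change | √(2(1 − ρ)) | 54.4% | 68.8% | 88.6% |
| T1 adjusted for T0 | √(1 − ρ²) | 72.9% | 80.8% | 92.9% |

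Power falls with ρ in the first row and rises in the other two. For the m = 3 calculation that yields 98, it also falls: at ρ = 0.7, λ = 18.375 / 2.4 = 7.66 and power is about 78%.

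**The case against.** The best defence is that 98 is a correct G*Power result for a design with three measurements, which is what Study design describes, and that the follow-up repeated measures ANOVA may use all three. This stands in part: **98 is not an arithmetic slip.** But the sample-size text says the calculation tests the mean over T1 and T2. No section names a group average that includes pre-treatment T0 as the quantity of interest.

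Several stronger readings are tempting, and the document does not support them:

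- *Three rival endpoints.* The hypothesis speaks of a lower mean after treatment and at 6 months, and the sample-size text may simply restate it. The firm conflict is T1 against T1 and T2.
- *The trial has 69% power.* That figure needs d = 0.5 at T1, equal baselines and ρ = 0.5. The article gives f and does not say on which scale. On G*Power's interaction scale the power is 99.8%.
- *The type I error is inflated.* If success at either T1 or T2 counted, the family-wise error would be about 9.1% (assuming a correlation of 0.5 between the tests). No section says either suffices. The hypothesis joins the two with an and, and requiring both would cause no inflation.
- *Calling ρ = 0.5 conservative is wrong.* It is not conservative for the between-groups average if the true correlation is higher, but it is for the T0–T1 interaction and for a baseline-adjusted T1 analysis. The label cannot be judged until a test is named.
- *A baseline-adjusted analysis is required.* Groups are formed by patient choice (Strengths and limitations) and have different entry criteria (Inclusion criteria). If they differ at T0, adjusted and change-score analyses can give different answers, so neither is the automatic choice.

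**Conclusion.** The point holds as an inconsistency between the endpoint, the deciding test and the basis of the sample size. The outcome section fixes T1, the hypothesis and sample-size text use T1 and T2, and the two primary analyses are unranked.

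Of the set-ups tried, the stated 85% at N = 98 fits only a three-measurement between-groups average that includes T0. For the T1/T2 mean named as its basis, the shortfall is about 4 points (80.8%) or 12 participants (110 − 98). For the T0–T1 interaction the mismatch may go either way: 68.8%, with a range of 54% to 89% over ρ from 0.3 to 0.7, if f = 0.25 means 0.5 SD at T1 with equal baselines; 99.8% if it is the interaction f. In neither case does 98 follow from 85%.

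These figures take 98 as the number analysed, with equal groups and equal variances. They do not show that the trial is too small. They show that its power has not been stated for the test that decides it.

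**What to change.** 1. Name one primary endpoint and one deciding test, worded identically in Primary hypothesis, Primary outcome, the sample-size text and the analysis text. T1 is the simplest choice, because Primary outcome and the first analysis already use it.
2. Make the other time point secondary and test it only if the primary result is significant.
3. Restate the power at the planned N for that test. Say what the effect size means (SD difference at T1, difference in change, or G*Power's interaction f) and how many measurements enter. Show a range of ρ in place of an unqualified claim that 0.5 is conservative.
4. Fix in advance whether the deciding test uses change from T0 or adjusts for T0. Adjusting T1 for T0 gives about 81% at 98 under the same assumptions (d = 0.5, ρ = 0.5, equal baselines). It is an option, not a requirement. If the sponsor prefers the T1/T2 mean, the unadjusted figure is 80.8%. Adjusted for T0, the residual variance is 0.75 − 0.25 = 0.5, the noncentrality is 2.475 / √0.5 = 3.5, and power is about 93%.

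The cost is an amendment to the wording and the registry entry, and possibly a less favourable stated power. No extra patients are needed.

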**Methods and analysis:**

This study presents a non-randomized controlled trial aimed at evaluating the effectiveness of a five-week multimodal inpatient psychosomatic treatment program for individuals experiencing PASC symptoms and comorbid mental illness. A total of 118 patients presented at the Post-COVID Center at the Universitätsklinikum Erlangen will be assigned to the intervention group receiving inpatient psychosomatic treatment or the control group receiving treatment as usual. The inclusion criteria for the intervention group are a diagnosis of PASC and at least one condition of mental distress and problems with coping with illness. The primary objective of the intervention is to reduce mental ailments, including depression and anxiety, as well as neurocognitive deficits, and to address PASC symptoms such as fatigue and pain. The core elements of the treatment are psychotherapy in individual and group settings, medical treatment, neurocognitive training, and physical therapy, adapted to the individual’s capacity and oriented towards the concept of pacing. After enrollment, participants will undergo a 6-month follow-up to assess long-term results and the sustainability of the intervention effects.

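### The enrolment sentence does not add up: 58 per group is 116, not 118; neither total leaves the required 98 after 20% dropout; and it says patients are randomised.

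*Protocol article*

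**What the plan says.** All the figures are in the protocol article, under *Sample size calculation and statistical methods*. For an effect size of f = 0.25 and 85% power, the section states that "a sample size of 98 participants is required, with 49 participants per group". It then sets the enrolment target: "Assuming a conservative dropout of 20%, we will randomize 118 participants, 58 for each condition". The abstract gives the same total: "A total of 118 patients presented at the Post-COVID Center".

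On allocation, *Study design* states: "This is a prospective non-randomized controlled trial". The title, the abstract and the Discussion say the same. *Strengths and limitations* adds that patients' own choice decides who is in the control group, and it names self-selection as a limitation.

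**The concern.** The enrolment total, the number per group and the dropout allowance are given in one sentence and should follow from each other and from the required 98. They do not. Two equal groups of 58 do not make 118. The total also looks as if 20% was added to the required number, when it should have been set so that 80% of those enrolled equals the required number.

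A reader cannot tell whether the target is 116 or 118, and neither provides the protection against dropout that the protocol claims. These are the planned numbers against which recruitment and the final report will be judged. Separately, the verb in the sentence describes an allocation method the trial does not use, and allocation is the design feature that most limits how its result can be interpreted.

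**Working it through.** **Inputs**, all from the protocol article:
- Required number: 98, or 49 per group; f = 0.25; power 85% (*Sample size calculation and statistical methods*).
- Correlation among repeated measurements: 0.5 ("we assumed a conservative correlation of 0.5 among repeated measurements and a medium effect size").
- Significance level: "In all analyses, two-sided p values of < 0.05 are considered to indicate statistical significance".
- Design: "It is a two (group: intervention and control) by three (time: pre-treatment, 5 weeks, 6 months) repeated measures factorial design".
- Dropout 20%; enrolment 118; 58 per condition (the sentence at issue).

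**1. Reproducing the required 98.** For the between-group effect in a repeated-measures ANOVA with m measurements and correlation ρ, the noncentrality is λ = f² × N × m / (1 + (m − 1)ρ), with 1 and N − 2 degrees of freedom. With m = 3, ρ = 0.5 and N = 98, λ = 0.0625 × 98 × 3 / 2 = 9.19 and power is 85.1%. This is the smallest even N that reaches 85%, so 98 reproduces with three measurements. The section does not state m; three is inferred because it returns 98.

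**2. Per-group figure against the total.** 2 × 58 = 116. A total of 118 needs 59 per group.

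**3. Where 118 comes from.** 98 × 1.2 = 117.6, which rounds up to 118. The same step per group gives 49 × 1.2 = 58.8, which is 59 rounded up; 58 appears only if it is cut down.

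**4. The correct allowance.** If a share d of those enrolled is lost, enrolment must be N / (1 − d):
- Total: 98 / 0.8 = 122.5, so 123.
- Equal groups: 49 / 0.8 = 61.25, so 62 per group and 124 in total.

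**5. What the stated targets deliver.** Power is from the model in step 1 with m = 3.

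| Enrolled | Left after 20% loss | Shortfall against 98 | Dropout that still leaves 98 | Power |
|---|---|---|---|---|
| 118 | 118 × 0.8 = 94.4 | about 4 | 1 − 98/118 = 16.9% | 83.6% at N = 94 |
| 116 | 116 × 0.8 = 92.8 | 5 to 6 | 1 − 98/116 = 15.5% | 82.8% at N = 92; 83.2% at N = 93 |

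**6. Allocation wording.** The sample size sentence says participants will be randomised. The title, abstract, *Study design* and Discussion all call the trial non-randomised, *Control group* defines controls as patients who do not take up the inpatient treatment, and *Strengths and limitations* attributes allocation to patient choice. The sample size sentence is the one out of line.

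**The case against.** The arithmetic is not open to dispute, but its weight is.

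- **The loss is small.** Power drops by 1.5 points at 94 completers and 2.3 at 92, much less than the uncertainty in an effect size and a correlation that the protocol says were assumed for want of data. This stands, and it limits how much the error matters for the trial's chance of success. It does not make the figures consistent.
- **The 58 is probably a slip for 59.** The total of 118 appears twice and 58 once. This is likely right, so 116 is the secondary case. The dropout error remains with 59 per group.
- **No reader would be misled about the design.** The non-randomised design is stated prominently and its bias is discussed. That is fair: the wrong verb is an editorial error. It still stands in the formal enrolment statement and contradicts the title.
- **Missing data will be imputed.** The section does plan this, so the number analysed need not be completers only, and completer-based power is a simplification. But the section presents the inflation as its allowance for dropout, and imputation does not make 118 × 0.8 equal 98.
- **The power figures depend on three measurements.** This objection has the most substance. The section describes the target as the mean over T1 and T2. With two measurements, f = 0.25 and ρ = 0.5, power is 80.8% at 98, 79.1% at 94 and 78.2% at 92, and 85% needs 110. Whether 98 is the right base is a separate question. Any power figure put into the corrected sentence must state the number of measurements it assumes.

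**Conclusion.** The enrolment sentence is wrong as written and must be corrected. The number per group contradicts the total by 2 patients. The 20% allowance is not provided: 118 falls short of the required 98 by about 4 patients and 116 by 5 to 6, and the dropout actually covered is 16.9% or 15.5%. The stated allocation method contradicts the rest of the protocol.

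The head counts rest only on the protocol's own 98, 20%, 118 and 58. The power loss, from 85.1% to 83.6% or 82.8%, also rests on f = 0.25, a correlation of 0.5, three measurements and an analysis of completers. The loss is modest, and the case for correction rests on the contradictions more than on lost power.

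**What to change.** Rewrite the sentence. The version that needs no more patients than the 118 already announced is:

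> We will enrol 118 participants (59 per group). This allows for about 17% dropout. With 20% dropout about 94 remain, and power is about 84% on the same assumptions (three measurements, correlation 0.5).

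If the primary test is redefined, or the calculation is redone for T1 and T2 only, replace the power figure with the one for that test.

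If the 20% allowance must hold in full, the target on a base of 98 is 62 per group (124 in total), which is 6 more than 118. That figure is correct only if 98 is kept as the base.

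In either version, *randomize* becomes *enrol*. The abstract's total needs changing only if 124 is chosen. The trial registry entry was not available for this review; it should be checked and aligned if it carries the same figures or wording.

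The cost of restating is one sentence and a slightly less favourable dropout and power statement.
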